# A randomised comparison of the effect of haemodynamic monitoring with CardioMEMS in addition to standard care on quality of life and hospitalisations in patients with chronic heart failure

**DOI:** 10.1007/s12471-019-01341-9

**Published:** 2019-11-27

**Keywords:** CardioMEMS, e‑Health, Heart failure, Telemonitoring, Therapy, Trial

## Abstract

**Background:**

Assessing haemodynamic congestion based on filling pressures instead of clinical congestion can be a way to further improve quality of life (QoL) and clinical outcome by intervening before symptoms or weight gain occur in heart failure (HF) patients. The clinical efficacy of remote monitoring of pulmonary artery (PA) pressures (CardioMEMS; Abbott Inc., Atlanta, GA, USA) has been demonstrated in the USA. Currently, the PA sensor is not reimbursed in the European Union as its benefit when applied in addition to standard HF care is unknown in Western European countries, including the Netherlands.

**Aims:**

To demonstrate the efficacy and cost-effectiveness of haemodynamic PA monitoring in addition to contemporary standard HF care in a high-quality Western European health care system.

**Methods:**

The current study is a prospective, multi-centre, randomised clinical trial in 340 patients with chronic HF (New York Heart Association functional class III) randomised to HF care including remote monitoring with the CardioMEMS PA sensor or standard HF care alone. Eligible patients have at least one hospitalisation for HF in 12 months before enrolment and will be randomised in a 1:1 ratio. Minimum follow-up will be 1 year. The primary endpoint is the change in QoL as measured by the Kansas City Cardiomyopathy Questionnaire (KCCQ). Secondary endpoints are the number of HF hospital admissions and changes in health status assessed by EQ-5D-5L questionnaire including health care utilisation and formal cost-effectiveness analysis.

**Conclusion:**

The MONITOR HF trial will evaluate the efficacy and cost-effectiveness of haemodynamic monitoring by CardioMEMS in addition to standard HF care in patients with chronic HF. Clinical Trial Registration number NTR7672.

**Electronic supplementary material:**

The online version of this article (10.1007/s12471-019-01341-9) contains supplementary material, which is available to authorized users.

## Introduction

In Western European countries such as the Netherlands, chronic heart failure (HF) is estimated to occur in 1.5–2.0% of the population [1, 2]. In the Netherlands, the prevalence was 227,000 patients in 2017, and the number of HF hospital admissions is high at 29,011 admissions per year with an average hospital stay of 9 days [1, 2]. The overall hospital burden from HF hospitalisations will rise rapidly in the coming decade due to aging of the population and better survival following myocardial infarctions. The main public and personal burden of HF is clustered in patients with New York Health Association (NYHA) functional class III and IV, who most often need to be hospitalised. Approximately 25% of all Dutch HF patients are in NYHA class III based on the latest CHECK HF registry findings [3]. Contemporary treatment of chronic HF shows a reasonably high adherence to European guidelines for the recommended drugs, when compared to US data in the CHAMP-HF registry [4, 5]. Still, both registries show considerable room for improvement in HF therapy considering target or optimal dosing of medication [4, 5]. So clearly, despite optimal medical treatment, there is a considerable residual risk, especially for patients in NYHA class III. The main problem for care givers and patients is timely recognition of a daunting cardiac decompensation and, if recognised, to react adequately and promptly.

Remote monitoring and telemonitoring initiatives have received wide attention for their promise in detecting early signs of decompensation and guiding HF therapy. Proactive guided treatment could optimise treatment further and prevent clinical deterioration. Such an approach could reduce HF hospitalisations and relieve the large burden of chronic HF exacerbations for the current health care systems. However, numerous telemonitoring programmes which were based on remote signs of clinical congestion such as weight or symptoms or impedance measurements through pacemakers have been largely disappointing [6–15]. From a physiological point of view, weight gain and symptoms of HF are late signs of an exacerbation of HF. New management strategies should focus on markers preceding the exacerbation of HF. It has been recognised that a period of decompensation starts with a rise in (intracardiac) filling pressures. A chain of events from haemodynamic (asymptomatic) congestion transits to clinical congestion.

CardioMEMS (Abbott Inc., Atlanta, GA, USA) is a small sensor capable of measuring pressures in the pulmonary artery (PA) on a daily basis. PA pressures can be used as an invasive haemodynamic surrogate marker of filling pressures, which has been shown to precede a period of decompensation for several weeks. This time window would allow the physician to intervene before clinical symptoms arise and act in a proactive way to avert an exacerbation of HF by adjusting the dose of diuretics or vasodilators. In line with this hypothesis, the CHAMPION trial in the USA demonstrated a significant 37% reduction in HF hospitalisations with PA monitoring applied in addition to standard care in patients with chronic HF [16, 17]. Observations in post-marketing studies (with historical controls) were consistent and confirm the low-risk and safe procedure as well as the durability of the device [17–20]. Despite the innovation in patient management, several profound differences exist in the organisation of HF care (HF outpatient clinic and HF nurses), level of standard care, as well as financial structure of the health care systems in Europe and the USA, which mean that the results of this one trial cannot be translated directly. Additionally, individual trial data in a European setting are lacking and clinical and financial data can only be extrapolated from US data [21, 22], in the knowledge that the costs and setup of the US health care system are not comparable to the European situation. We therefore designed the MONITOR HF randomised clinical trial to evaluate the effectiveness and cost-effectiveness from a European perspective in the Netherlands.

## Methods

### Study design

The MONITOR HF trial is an investigator-initiated, multicentre, randomised clinical trial enrolling 340 patients with chronic HF NYHA class III and at least one HF hospitalisation in the previous 12 months. In total, 20 Dutch hospitals, distributed over the country, agreed to participate (Fig. 1; Electronic Supplementary Material, Appendix Tab. 1). Sites without previous experience with CardioMEMS will go through a learning curve of two patients for sensor implantation and pressure management, who do not participate in the main trial but are followed according to study protocol. Alternatively, added centres can proctor two patients in an experienced centre. The MONITOR HF trial aims to test the effect of PA monitoring in addition to standard HF care on quality of life (QoL), the number of HF hospitalisations and cost-effectiveness in a Dutch health care system. Four populations for analysis are defined in the MONITOR HF trial: intention-to-treat, as-treated and per-protocol (time until implant after randomisation (maximum 3 weeks per protocol)) and safety analysis. The principal analysis for the primary effectiveness endpoint will be performed in the intention-to-treat population.

**Fig. 1 Fig1:**
[figure not shown]
Participating centres in the Netherlands

**Table 1 Tab1:** Inclusion criteria. In order to be eligible to participate in this study, a subject must meet all of the following criteria

1	Written informed consent obtained from subject aged ≥18 years
2	Diagnosis of chronic heart failure^a^ (≥3 months) in NYHA functional class III with 1 HF hospitalisation within 12 months (defined as an admission for HF longer than 6 h and/or use of i.v. diuretics) or emergency ward visit for HF resulting in i.v. diuretic therapy (independent of EF %)
3	HF subjects with reduced EF (HFrEF) should be treated according to national and international (ESC) guidelines for optimal or maximum tolerated doses of HF medication and evaluated for ICD or CRT‑D therapy, if indicated
4	Subjects with a BMI ≤ 35. Subjects with BMI > 35 will require their chest circumference to be measured at the axillary level < 65 inches or 165 centimetre (related to distance of the sensor to the pillow)
5	Subjects willing and able to comply with the follow-up requirements of the study and able to comply with the daily readings

^a^According to the definition given in the 2016 ESC guidelines for heart failure [10]. In line with good clinical practice, a patient cannot participate in any other interventional study or active telemonitoring programme (on HF parameters) during the study

*NYHA* New York Heart Association, *HF* heart failure, *EF* ejection fraction, *ESC* European Society of Cardiology, *ICD* implantable cardioverter-defibrillator, *CRT‑D* cardiac resynchronization therapy defibrillator, *BMI* body mass index

The MONITOR HF trial is sponsored by the Dutch Ministry of Health and National Health Care Institute (Zorginstituut, Nederland) as part of a conditional coverage programme in the Netherlands for the health-care-related costs. The study and data management are performed by the CRO Erasmus MC University Medical Centre (Sponsor).

### Type of patients

Patients with chronic HF (≥3 months) in NYHA functional class III and at least one hospitalisation for HF (or emergency ward visit resulting in intravenous diuretic therapy) in the 12 months prior to enrolment are eligible for the trial. The diagnosis of HF is made according to the criteria set out in the 2016 European Society of Cardiology (ESC) guidelines for the treatment of HF [23]. Patients with HF and reduced ejection fraction (HFrEF), mid-range (HFmrEF) or preserved ejection fraction (HFpEF) are eligible for the trial. The inclusion and exclusion criteria are presented in Tab. 1 and 2.

**Table 2 Tab2:** Exclusion criteria

1	Subjects with an active infection
2	Subjects with a history of recurrent (>1) pulmonary embolism or deep vein thrombosis
3	Subjects who have had a major cardiovascular event (e.g. myocardial infarction, open heart surgery, stroke) within the past 2 months
4	Subjects with a CRT implanted <3 months prior to enrolment and implantation of the sensor (in order to avoid manipulation of lead)
5	Subjects with an estimated GFR < 25 ml/min (obtained within 2 weeks of the baseline visit), refractory to diuretic therapy, or on chronic renal dialysis
6	Subjects with complex congenital heart disease or mechanical right heart valve(s)
7	Subjects with known pulmonary arterial hypertension (WHO category 1 or 4/5) in whom PA pressure is most likely not responsive to cardiac treatment
8	Subjects scheduled for or likely to undergo heart transplantation or receive a ventricular assist device within 6 months of baseline visit
9	Subjects with known coagulation disorders or allergy to acetylsalicylic acid and/or clopidogrel

*CRT* cardiac resynchronisation device, *GFR* glomerular filtration rate, *PA* pulmonary artery

### Randomisation

At the baseline visit, patients will be randomised in a 1:1 ratio for standard care plus CardioMEMS PA monitoring versus standard HF care with written and signed informed consent. Crossover is not allowed per study protocol and leads to termination of the patient’s participation in the study. After randomisation, the sensor is to be implanted within 3 weeks per protocol in those randomised to CardioMEMS and a second informed consent form will be signed for use of the Merlin.net website.

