#### Duration of follow-up

All patients will be followed for at least 12 months, resulting in a minimum follow-up of 12 months (for the last patient included) and a maximum follow-up of 36 months (for the first patient included) according to the above-mentioned enrolment schedule. The follow-up visits are scheduled at 3, 6, and 12 months and every 6 months thereafter (Fig. 3).

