### Outcome measures

#### Primary endpoint: Change in QoL as assessed with the KCCQ HF questionnaire

The KCCQ questionnaire is conducted at baseline (*t* = 0), and at follow-up intervals of 3, 6 and 12 months’ follow-up after randomisation in both treatment arms. Primary analysis is based on change in KCCQ scores at 12 months (Tab. 4). The KCCQ questionnaire assesses QoL in HF patients and has undergone extensive validation in HF populations [27, 28].

**Table 4 Tab4:** Study endpoints

Primary endpoint	Quality of life as measured by the KCCQ HF questionnaire at 12 months’ follow-up
Secondary endpoint	The number of HF hospitalisations during follow-up
	Health status as measured by the EQ-5D-5L questionnaire

*KCCQ* Kansas City Cardiomyopathy Questionnaire, *HF* heart failure

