#### Data analysis

Data will be summarised using univariate statistics (number, mean, standard deviation, median) or frequency (number, percentage). For baseline characteristics, between-group comparisons will be performed with the χ2 test for categorical variables and two-sample *t*-tests for continuous variables. The primary time-point for effectiveness analyses on improvement of QoL is 12 months. Change in the KCCQ-OS from baseline to 12 months will be compared between the intervention and standard care groups. Additionally, a linear mixed-effects model will be used to compare change in the KCCQ-OS over time between the randomly allocated treatment groups to account for missing data and longitudinal trends. The effect of CardioMEMS in comparison to standard care in changes of KCCQ clinical summary and KCCQ-OS scores is compared using repeated measurement analysis of covariance adjusted for baseline KCCQ score. EQ-5D-5L scores will be analysed in a comparable manner. The secondary endpoint in the study is the number of HF hospitalisations during follow-up. A Cox proportional hazard regression model with Anderson-Gill method for recurrent events will be used for analysis of clinical events (HF hospitalisations, mortality rates). Additionally, Cox proportional hazard models are implemented to analyse time to first events, including mortality and hospitalisation. Hospitalisation rates and mortality rates are estimated using the Kaplan-Meier method, and *p*-values are computed using the log-rank test. All reported analyses are performed using the intention-to-treat principle. All statistical tests will be 2‑sided with a significance level of 0.05.

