### Strengths and limitations

The current trial is important as it is the first randomised clinical trial in Europe comparing haemodynamic remote monitoring by CardioMEMS with a control group in chronic HF. The trial is adequately powered to test the efficacy of CardioMEMS (in addition to standard care) in improving QoL and reducing HF hospitalisations as compared to standard care. Additionally, this trial will provide further contemporary data with CardioMEMS in addition to the CHAMPION trial and post-marketing registries. As randomisation is essential in efficacy studies (but lacking in post-marketing studies), the current European trial is the first with a control group of standard HF care after the US CHAMPION trial. This MONITOR HF trial will not have a sham procedure in consultation with the MEC and patient councils for a variety of reasons. A sham procedure and sham measurements every day during 3 years of follow-up was deemed unethical with a futile risk, patient efforts and costs. Furthermore, we argue that daily sham measurements (with the sensor turned off, but with its costs) are not a part of current standard care and would impact the true comparison with standard care as it is actually delivered. We recognise that the lack of a sham procedure may introduce a potential bias in the standard care arm. However, this effect can be of any magnitude, direction and degree for each individual patient, either positive or negative (as the technique is most likely not suited for all), and therefore it will be complex to completely quantify the placebo effect (and directions). We will keep precise track of medication changes in response to abnormal readings of PA pressure and HF admissions as well as detailed records of health care utilisation rates, to provide objective proof of subjective improvements. Finally, despite the mentioned limitations, proactive monitoring and interventions based upon pre-symptomatic pressure shifts are needed to achieve any actual sustained benefit of the device. The design of the current trial and the involvement of HTA experts from the start of the project ensures high-quality data for future cost-effectiveness analyses and modelling from a Western European perspective, including detailed health care utilisation data.

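### Ending study participation at crossover conflicts with the intention-to-treat analysis and with the follow-up promised for every patient

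*Protocol article*

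**What the plan says.** The Randomisation section of the protocol article states: "Crossover is not allowed per study protocol and leads to termination of the patient’s participation in the study". The wording ends participation in the study, not only use of the allocated strategy.

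Three other statements bear on this rule:

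- Study design: "The principal analysis for the primary effectiveness endpoint will be performed in the intention-to-treat population".
- Data analysis: "All reported analyses are performed using the intention-to-treat principle".
- Duration of follow-up: "All patients will be followed for at least 12 months, resulting in a minimum follow-up of 12 months". No exception is made for patients who cross over.

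The primary endpoint section fixes the time point: "Primary analysis is based on change in KCCQ scores at 12 months". KCCQ is also collected at 3 and 6 months. Data analysis adds a linear mixed-effects model "to account for missing data and longitudinal trends". Nothing in the article says that questionnaires, admissions or deaths are still collected once a patient has crossed over.

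**The concern.** Intention-to-treat needs outcomes on every randomised patient, whatever care is later received. A rule that ends participation at crossover makes outcome data depend on an event after randomisation. The trial is open ("This MONITOR HF trial will not have a sham procedure"), so patients and clinicians know the arm and can act on it. A decision to switch is then plausibly tied to how the patient is doing.

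If so, the lost outcomes are not a random sample. The comparison of change at 12 months would leave these patients out or depend on untested assumptions about them. The recurrent-event and time-to-first-event models would censor them at the moment of switching as if that moment carried no information. The EQ-5D-5L and survival inputs to the cost-effectiveness model would be cut short in the same way.

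**Working it through.** **1. The plan's own figure.** Inputs from Sample size: difference 6 points, SD 15, alpha 0.05 two-sided, power 90%. The normal approximation is n per arm = 2(1.960 + 1.282)² × 15² / 6² = 131.3, so 132. The t-test version gives 132.3, so 133. The stated 133 per arm (266 in total) reproduces.

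**2. Power is not the main problem.** With 340 patients (170 per arm), the standard error of the difference is 15 × √(2/170) = 1.63 and power is 95.8%. With 10% lost (153 per arm), it is 15 × √(2/153) = 1.715 and power is 93.8%. The issue is bias.

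**3. KCCQ shift.** Let c be the share of one arm that crosses over and leaves. Let k be how many points worse their 12-month change would have been, had it been recorded, than that of the patients who stay. The full arm mean equals the stayers' mean minus c × k, so dropping these patients shifts the arm mean by c × k. The documents give neither c nor k; all values below are assumptions.

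| c | k (points) | shift (points) | share of the 6-point target |
|---|---|---|---|
| 2% | 5 to 15 | 0.1 to 0.3 | 2% to 5% |
| 5% | 10 | 0.5 | 8% |
| 5% | 15 | 0.75 | 12.5% |
| 10% | 10 | 1.0 | 17% |
| 10% | 15 | 1.5 | 25% |

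If the true effect is zero and 153 per arm are analysed, the two-sided error rate under a shift b is Φ(b/1.715 − 1.96) + Φ(−b/1.715 − 1.96). This gives about 7% for b = 0.75, 9% for b = 1.0 and 14% for b = 1.5, against 5% nominal. Losing poorly performing controls pushes the estimate against the device. Losing poorly performing device patients pushes it in favour.

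**4. Heart failure admissions.** From the article: control rate 2.0% per month, treatment effect 33% (rate ratio 0.67), 170 per arm, follow-up from 12 to 36 months (midpoint 24). Assumed: 5% of controls cross over at 6 months on average, and without the device would have had three times the average rate over the remaining 18 months.

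- Control events without crossover: 170 × 24 × 0.02 = 81.6 in 4,080 patient-months.
- Removed by termination: 8.5 × 18 × 0.06 = 9.2 events and 8.5 × 18 = 153 patient-months.
- Control rate as observed: (81.6 − 9.2) / (4,080 − 153) = 0.0184.
- Device-arm rate: 0.67 × 0.02 = 0.0134.
- Rate ratio with termination: 0.0134 / 0.0184 = 0.73.

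The right comparator is what full intention-to-treat follow-up would show. If the device works in switchers, their 9.2 events become 9.2 × 0.67 = 6.2. The control rate is then (72.4 + 6.2) / 4,080 = 0.0193 and the rate ratio 0.0134 / 0.0193 = 0.70. It would be 0.67 only if switching had no effect on the controls' events. Under these assumptions the termination rule moves the estimate from about 0.70 to about 0.73.

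**5. What the planned models can recover.** Suppose worsening shows in the 3- or 6-month KCCQ before the patient leaves. The later loss is then missing at random given those scores, and a likelihood-based mixed model can address it. Worsening between visits that no score captured stays uncorrected. The mixed model is described as additional to the 12-month comparison. The Cox and Andersen-Gill analyses have no comparable provision.

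**The case against.** The best counter-argument is that crossover may be rare. The Abstract says the sensor is not reimbursed in the European Union, and Study design ties the health-care costs to a conditional coverage programme, so a control patient has a narrow route to the device. At 2% crossover the shift is negligible. Even 0.75 points is under half a standard error (0.75 / 1.63 = 0.46). That crossover is selective is an inference, not something the documents report. The full protocol, which is not shown, may also separate stopping the strategy from stopping follow-up. All of this stands, and it limits the size and urgency of the point. It does not reconcile the sentences: the article states termination of participation and does not merely leave out a detail.

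Several stronger readings are tempting, but the documents do not support them:

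- *The principal analysis becomes a per-protocol analysis.* Nothing says that data before crossover are discarded or that these patients leave the intention-to-treat set. Ending follow-up creates missing data; it does not redefine the population.
- *The as-treated population is useless.* Study design states: "Four populations for analysis are defined in the MONITOR HF trial: intention-to-treat, as-treated and per-protocol". The as-treated set can still reclassify patients who were never implanted. It loses only data from after a crossover.
- *A missed, late or refused implant counts as crossover.* The article does not say so. The per-protocol population is defined by time to implant, which suggests that patients outside the 3-week window remain in the trial.
- *The mixed model gives no protection.* It protects where earlier scores explain the loss.
- *The admissions bias should be measured from 0.67.* That ignores any device benefit in controls who switch. About 0.70 is the fair comparator in the illustration.

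**Conclusion.** The concern holds as a conflict between stated rules. Termination at crossover is incompatible with intention-to-treat as the principal analysis and with at least 12 months of follow-up for all, and the planned analyses would only partly make up for the lost outcomes.

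The size cannot be determined, because no crossover rate, direction or prognosis of switchers is given. On assumed inputs it runs from negligible (2% of one arm) to a quarter of the target KCCQ difference (10% with a 15-point gap). For admissions it is a move in the rate ratio from about 0.70 to about 0.73. The worked admissions case is conservative, since it removes the worst controls; bias in the other direction needs loss from the device arm.

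This merits a correction because it is cheap and because follow-up that was not collected generally cannot be recovered at analysis. It is not a demonstrated threat to the primary result.

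**What to change.** Replace the termination clause with wording such as: *Crossover is a protocol deviation. Patients who cross over remain in follow-up for all visits, questionnaires and events and are analysed in the arm to which they were randomised. Data collection ends only on withdrawal of consent, death or study end.*

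The prohibition on crossover itself need not change. If the full protocol already keeps these patients in follow-up, it is enough to align the Randomisation text with it.

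The cost is one sentence in a minor amendment, plus continued follow-up of what is probably a small number of patients already enrolled. The sample size does not change.
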